## Abstract

**Background:**

A scaphoid fracture is the most common type of carpal fracture affecting young active people. The optimal management of this fracture is uncertain. When treated with a cast, 88 to 90 % of these fractures unite; however, for the remaining 10-12 % the non-union almost invariably leads to arthritis. The alternative is surgery to fix the scaphoid with a screw at the outset.

**Methods/Design:**

We will conduct a randomised controlled trial (RCT) of 438 adult patients with a “clear” and “bicortical” scaphoid waist fracture on plain radiographs to evaluate the clinical effectiveness and cost-effectiveness of plaster cast treatment (with fixation of those that fail to unite) versus early surgical fixation. The plaster cast treatment will be immobilisation in a below elbow cast for 6 to 10 weeks followed by mobilisation. If non-union is confirmed on plain radiographs and/or Computerised Tomogram at 6 to 12 weeks, then urgent surgical fixation will be performed. This is being compared with immediate surgical fixation with surgeons using their preferred technique and implant. These treatments will be undertaken in trauma units across the United Kingdom. The primary outcome and end-point will be the Patient Rated Wrist Evaluation (a patient self-reported assessment of wrist pain and function) at 52 weeks and also measured at 6, 12, 26 weeks and 5 years. Secondary outcomes include an assessment of radiological union of the fracture; quality of life; recovery of wrist range and strength; and complications. We will also qualitatively investigate patient experiences of their treatment.

**Discussion:**

Scaphoid fractures are an important public health problem as they predominantly affect young active individuals in the more productive working years of their lives. Non-union, if untreated, can lead to arthritis which can disable patients at a very young age. There is a rapidly increasing trend for immediate surgical fixation of these fractures but there is insufficient evidence from existing RCTs to support this. The SWIFFT Trial is a rigorously designed and adequately powered study which aims to contribute to the evidence-base to inform clinical decisions for the treatment of this common fracture in adults.

**Trial registration:**

The trial is registered with the International Standard Randomised Controlled Trial Register (ISRCTN67901257). Date registration assigned was 13/02/2013.

## Background

Scaphoid fracture is the most common carpal fracture and is an important public health problem as it predominantly affects young active individuals (mean age 29 years [1]) in their most productive working years. These fractures account for 2 to 7 % of all fractures [2]. However, 10 to 12 % do not unite when treated with plaster cast, with a higher incidence of non-union (14 to 50 %) in displaced fractures [3–5]. Non-union, if untreated almost inevitably leads to arthritis, usually within 5 years of injury [6, 7]. This can potentially disable patients at a relatively young age.

Recent systematic reviews [8–12] have found insufficient evidence from randomised controlled trials (RCTs) to inform clinical decisions on the treatment of scaphoid waist fractures. Eight small RCTs comparing surgery with non-operative management [12] could not establish whether patients who had surgical fixation of undisplaced or minimally displaced scaphoid fractures had better longer term outcomes. Surgery in these RCTs was shown to facilitate early return of function, but had a higher complication rate (between 9 and 22 %) compared with conservative management although the complications were usually minor [1, 13, 14]. The rate of union was similar between surgical and cast treatment with early fixation of those fractures that failed to unite [1]. A further study found similar outcomes at 10 years [15].

Despite insufficient evidence there is a rapidly increasing trend [16] for immediate surgical fixation compared to cast immobilisation for 6 weeks and fixing only those 10 to 12 % that fail to unite [1]. This current trend to fix fractures may be attributed to potential short-term benefits, but concerns remain about the lack of evidence on long-term benefits and additional risks from surgery, such as malunion, infection, implant related problems and avascular necrosis (AVN).

Hospital Episode Statistics (HES) for National Health Service (NHS) hospitals in England recorded a near doubling (1534, 1720 and 2582) of acute scaphoid fracture fixations for the years 2007/8, 2008/9 and 2009/10 respectively. In each of these three years we calculated an expected incidence of scaphoid waist fractures of 4140, 4169 and 4197 (population of 51.1, 51.4 and 51.8 million respectively in England in 2007, 2008 and 2009 and based on a rate of 81 acute scaphoid fractures/million population per year) [17]. We had to estimate this as currently the diagnosis of cases that do not receive surgical treatment, or those treated only in the outpatient setting, are not recorded in HES. The rate of surgical fixation [18] rose very slightly from 37 to 41 % from 2007/8 to 2008/9 but then increased sharply to 62 % in 2009/10. This trend of increasing intervention rate for these fractures emphasises the urgent need for this study.

Little is published on patient experiences after a scaphoid fracture and issues pertinent to recruiting participants into surgical RCTs [19, 20]. There is also poor information on the economic aspects [21] of this injury and its treatment.

These limitations, identified in the current evidence base, justify this adequately powered study. It will contribute to the evidence base for sound clinical decisions for the treatment of this common fracture in predominantly young adults.

## Methods/Design

### Design

This is a pragmatic, multi-centre RCT, investigating whether immediate surgical fixation of minimally displaced fractures of the scaphoid waist leads to better patient reported outcomes when compared to initial non-operative treatment with later surgical fixation of only those fractures that fail to unite. The study includes an economic analysis and has a nested qualitative study to explore patient experiences of their treatment. The objectives are listed in Table 1.

**Table 1 Tab1:** SWIFFT trial objectives

Objectives	
1	Our primary objective is to determine the effectiveness of surgical fixation versus non-operative plaster cast treatment (with fixation of those that fail to unite, estimated as 10 % to 12 % of the total) of scaphoid waist fractures in adults. Outcome will be assessed using the PRWE (a patient self-reported assessment of wrist pain and function) at 52 weeks which will be the primary end point. The PRWE will also be completed at 6, 12, 26 weeks and 5 years. The power of the study permits identification of a clinically meaningful difference of 6 points in the PRWE.
2	To assess secondary outcomes of radiological union of the fracture at 52 weeks using radiographs and CT scans; recovery of wrist range and strength; return to work and recreational activities and; complications.
3	To conduct an economic analysis to investigate the cost-effectiveness of surgical fixation versus initial immobilisation in a plaster cast.
4	To qualitatively explore patient experiences of the fracture and its treatment; and investigate attitudes towards, and experiences of, participating in a surgical, clinical research trial.
5	To undertake a 5 year clinical review of all trial participants to determine the long-term consequences of cast immobilisation and internal fixation.

The trial is registered as ISRCTN67901257 and can be found by searching at http://www.isrctn.com/ at the time of registration we were not explicit that the pain and function sub-scales of the primary outcome would be included as secondary outcome measures, this had been included in the grant application.

### Study participants

Patients are eligible for this study if theyare skeletally mature and aged 16 years old or abovepresent at a participating site within two weeks of their injuryhave a clear, unequivocal bicortical fracture of the scaphoid waist confirmed on a series of plain radiographs of the scaphoid whichdoes not involve the proximal pole (proximal fifth of the scaphoid) andis minimally displaced with less than or equal to 2 mm step or gap on any view.

Patients will be excluded from this study iftheir fracture has >2 mm displacement as these are likely to be unstablethey have a concurrent wrist fracture in the opposite limbthey have a trans-scaphoid perilunate dislocationthey have multiple injuries in the same limbthey lack mental capacity to comply with treatment or data collectionthey are pregnant because radiation exposure would be contraindicatedthey are not resident in the trauma catchment area of a participating site to allow follow-up.

### Trial interventions

#### Cast treatment

Control treatment is non-operative with immobilisation in a below elbow cast for 6 to 10 weeks, followed by mobilisation. Pragmatically we have not specified whether the thumb should be included in the cast as this does not affect union rate [3], but we will record the type of cast used. Early Computerised Tomogram (CT) will be obtained at the discretion of the treating surgeon if plain radiographs at 6 to 12 weeks raise the suspicion of non-union which we expect in 10 to 12 % of non-operatively treated patients. If non-union is confirmed on radiographs and/or CT scan, urgent surgical fixation will be performed. The surgical procedure and post-operative care will be similar to the surgical arm of this trial. This is the current standard non-operative pathway [1].

#### Surgery

Immediate surgical fixation avoids the need to immobilise the wrist in a cast and may accelerate return of function [22] but requires the individual to have surgery and be exposed to surgical risks.

Surgical treatment is by percutaneous or open surgical fixation with standard CE marked headless compression screws [14, 23, 24] which avoid the pressure effects of the screw head on articular cartilage. The surgical techniques are well described and are now standard [25–27]. We will not restrict the type of implant used but will record what screw was used. We will not specify the surgical approach or the postoperative care as most surgeons currently use some splintage for the first few weeks after surgery. It will be agreed at each recruiting site which surgeons will fix the scaphoid fractures and that these surgeons should use techniques with which they are familiar.

#### Rehabilitation

All patients randomised into the two groups will receive standardised, written physiotherapy advice detailing the exercises they need to perform for rehabilitation following their injury. All patients in both groups will be advised to move their shoulder, elbow and finger joints fully within the limits of their comfort. Those patients treated in a cast will perform range-of-movement exercises at the wrist as soon as their plaster cast is removed at the 6-week follow-up appointment if there are no concerns regarding bone union. Those patients who have the fracture fixed may begin wrist exercises as soon as comfort permits if they do not have a plaster cast or as soon as the cast is removed. In this pragmatic trial, any other rehabilitation input beyond the written information sheet (including a formal referral to physiotherapy) is at the discretion of the treating surgeon. However, a record of any additional rehabilitation input (type of input and number of additional appointments) is to be recorded at the 52 week follow-up.

### Outcome measures

Table 3 outlines the time points where various outcomes are assessed. These outcomes are described below.

**Table 3 Tab3:**
[figure not shown]
Timescale of enrolment, interventions and follow-ups for patients

^a^Where possible the CT should be done before randomisation, if this is not feasible it must be scheduled before surgery and must be done within two weeks of a patient’s injury

^b^Patients allocated to surgery must receive this within two weeks from when the patient presents to A&E or other point of contact (e.g. walk-in centre, cottage hospital)

^c^Patients are initially put into plaster cast for 6 to 10 weeks. If non-union is confirmed on X-rays/CT at 6 or 12 weeks urgent surgical fixation will be performed

^d^These X-rays/CT are those routinely collected whereas at the other time-points are compulsory

### Primary outcome

The primary outcome and end-point for the trial is the Patient Rated Wrist Evaluation (PRWE) total score at 52 weeks from randomisation.

### Patient rated wrist evaluation

The PRWE is completed at baseline for the time before and after injury, and at 6, 12, 26, 52 weeks and 5 years after randomisation. The PRWE is a 15-item questionnaire that is completed by the patient. It is a brief, reliable and valid instrument for assessing wrist pain and disability [28, 29]. Scoring for all the questions is on a 10-point, ordered scale ranging from ‘no pain’ or ‘no difficultly’ (0) to ‘worst ever pain’ or ‘unable to do’ (10). Two non-overlapping subscales are generated: pain and function and a total score can be computed on a scale of 0 to 100 (0 = no disability) where pain and function domains are weighted equally.

PRWE has been chosen as the primary outcome as patient reported functional outcomes are favoured for decision making and it allows assessment of both wrist pain and function.

### Timing of primary outcome

Two small RCTs [1, 14] of patients with fractures of the scaphoid have demonstrated that there is little change in objective and subjective outcomes between 26 and 52 weeks. For the 10 to 12 % of patients who are treated initially in cast but do not heal, surgery should be performed between 6 and 12 weeks from randomisation. Therefore, if assessed at 26 weeks this would leave only 14 to 20 weeks for healing and recovery to take place. To allow all patients the time to heal from surgery and recover from complications we have chosen 52 weeks as the primary end point.

### Secondary outcomes

#### Patient rated wrist evaluation

PRWE total scores at other time points (6, 12, 26 weeks and 5 years) as well as the PRWE subscale scores of pain and function will be secondary outcomes.

### Short form 12-item questionnaire (SF-12)

The SF-12 is a 12 item generic patient-reported outcome measure of physical and mental health, the population norms of which have a mean of 50 and standard deviation of 10; higher scores indicate better health [30]. The SF-12 is completed at 6, 12, 26 and 52 weeks and at 5 years to measure the potential broader consequences of a scaphoid fracture on both the participants’ physical and mental health.

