### EuroQol (EQ-5D-3L)

The EQ-5D is a validated, generic patient-reported outcome measure covering five health domains (mobility, self-care, usual activities, pain/discomfort and anxiety/depression). We will use the original EQ-5D which contains three response options within each of the five domains [31, 32]. The use of this non-fracture-specific instrument will allow us to assess health-related quality of life outcomes in the health economic analysis. The EQ-5D has high validity and reliability in proximal humerus fractures [33] and hip fractures [34]. The EQ-5D is completed at baseline, 6, 12, 26 and 52 weeks.

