### Sample size

For surgery to justify its increased costs and the exposure to risk, it must result in greater or quicker improvement in patients’ wrist symptoms and function compared with non-operative management. We judge that a 6 point improvement in the PRWE in the surgery group (compared to the controls) would be a minimal clinical important difference. We estimate the standard deviation of PRWE at 52 weeks to be 20 points from the PRWE User manual [54]. This figure is reported for distal radius fracture rather than scaphoid fracture at 6 months. The only published evidence for scaphoid fracture implies a standard deviation in the range of 8 to 10 points [15]; however, this estimate was at a median of ten years after the patient’s injury. To be conservative we have chosen the estimate of standard deviation to be 20, which gives a standard effect size of 0.3 for the 6 point PRWE difference.

We will use a superiority design to observe an effect size of 0.3 at 80 % power using a 2-sided 5 % significance level requiring 350 participants in total. After allowing for 20 % attrition we need to recruit and randomise 438 participants (219 surgery and 219 controls). The estimate of attrition is likely to be realistic given that four RCTs (three studies were single centre and one study had two centres) included in a systematic review of the treatment of scaphoid fractures found response rates for completion of patient-reported functional outcomes between 77 and 100 % [12].

To minimise attrition we will exclude the rare patient in this population who lacks mental capacity and therefore unlikely to comply with treatment or data collection. Active and systematic follow-up of all randomised participants will be conducted at 6, 12, 26 and 52 weeks when we will arrange for the questionnaire to be completed when the participant attends the clinic. An additional 5 year review is also planned. We will monitor the completion of questionnaires at clinics and share retention figures with each trial site blinded by centre.

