### Statistical analysis plan

A detailed analysis plan will be agreed with the Data Monitoring and Ethics Committee at an early stage of the study, before all of the data has been collected. Any subsequent amendments will be clearly stated and justified. All analyses will be conducted on an intention to treat basis, including all available randomised participants in the groups to which they were allocated. Analyses will be conducted using 2-sided significance tests at the 5 % significance level (unless otherwise stated). The statistician conducting the analyses will remain blind to treatment group until all data summaries and results are finalised. For some variables the type of data reveals treatment allocation (e.g. complication data), hence relevant analyses will be conducted by a second statistician.

The flow of participants through each stage of the trial will be presented in a CONSORT flow diagram [57]. PRWE scores will be summarised descriptively (number, mean, standard deviation, median, interquartile range, minimum and maximum) at each time point by treatment group and overall. PRWE at baseline will be collected for the time before and after injury. Mean pre-injury PRWE scores will be presented in total and for each treatment group and compared descriptively to PRWE scores post-injury at baseline and all other follow-up time points.

Our primary analysis will compare total PRWE scores between treatment groups at 52 weeks using a covariance pattern mixed model incorporating all post-randomisation time points, where effects of interest and baseline covariates are specified as fixed effects, and the correlation of observations within patients over time (random effect) is modelled by a covariance structure. The outcome modelled will be PRWE at 6, 12, 26 and 52 weeks, predicted by treatment group, time, treatment group-by-time interaction and adjusting for age, fracture displacement (undisplaced vs. minimally displaced) and hand dominance. Estimates of the difference between treatment groups in total PRWE scores will be derived at all time points with 95 % confidence intervals and *p*-values. The primary end point will be the treatment effect estimate at 52 weeks. This model will naturally include all patients who provide data for the baseline covariates, and valid PRWE data for at least one post-randomisation follow-up time point.

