The impact of missing PRWE outcome data will be minimised to some extent by using the mixed model, which allows the inclusion of intermittent responders in the primary analysis. PRWE scores for complete and intermittent responders will be compared descriptively. The impact of missing data will additionally be assessed using multiple imputation by chained equations. Missing outcome and covariate data will be predicted by age, fracture displacement, hand dominance, available PRWE data at other follow-up time points, and any baseline covariates found to be predictive of missing 12 month outcome data.

All secondary outcomes will be summarised descriptively. The following outcomes will be analysed using the same methods as the primary analysis adjusting for the same covariates: pain and disability subscales of the PRWE, physical health and mental health component summaries of the SF-12 and range and grip strength. Where available, baseline values of the dependent variable will also be included as a covariate in the models. The presence of any complication assessed by clinical examination up to 52 weeks will be analysed by logistic regression (sufficient numbers permitting). Complications will be defined as medical, surgical or plaster cast related. Union will be assessed as a percentage (0–100 %) and categorised as: total non-union [0 %]; slight union [>0–20]; partial union [>20–70]; mostly united [>70–<100]; and complete union [100 %]. Summary statistics for union will be presented at each time point by trial arm. Union will be dichotomised into a ‘Probably need surgery’ group [0–20 %] and a ‘Probably do not need surgery’ group [>20–100 %] and analysed using a logistic regression adjusting for treatment group.

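### No baseline SF-12 is listed, so neither SF-12 summary can be adjusted for its own baseline; this costs some precision but causes no bias

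*Protocol article*

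**What the plan says.** The protocol's SF-12 section sets the schedule: "The SF-12 is completed at 6, 12, 26 and 52 weeks and at 5 years". Baseline is not among the times. The same section describes the scale as one "the population norms of which have a mean of 50 and standard deviation of 10".

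The Statistical analysis plan section names the secondary outcomes to be fitted with the primary mixed model. Besides the PRWE subscales these include "physical health and mental health component summaries of the SF-12 and range and grip strength". The common covariate set is fixed by "adjusting for age, fracture displacement (undisplaced vs. minimally displaced) and hand dominance". For the secondary outcomes there is one addition: "Where available, baseline values of the dependent variable will also be included as a covariate in the models".

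The other instruments do have a baseline. For the primary instrument, "The PRWE is completed at baseline for the time before and after injury". For the other generic questionnaire, "The EQ-5D is completed at baseline, 6, 12, 26 and 52 weeks". The Objective measures section also places range of movement and grip strength at baseline. The Randomisation section has baseline forms completed after consent, at the point of randomisation.

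**The concern.** Among the outcomes assigned to this model, the SF-12 is the only one without a stated baseline, and the text gives no reason. The baseline-covariate rule therefore has nothing to act on for either summary.

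The three remaining covariates do not measure a patient's general physical or mental health. If such health differs between patients and persists over the year, part of the spread in SF-12 scores at follow-up could be explained by a baseline score. Without one, that part stays in the error term and the intervals for both treatment differences are wider than they need be. What is at stake is the precision of two secondary outcomes, included to capture effects of the fracture beyond the wrist.

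**Working it through.** **1. The plan's own figure.** The Sample size section uses a 6-point PRWE difference and an SD of 20, and states "effect size of 0.3 at 80 % power using a 2-sided 5 % significance level requiring 350 participants in total".

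- Per arm: n = 2 × (1.960 + 0.842)² × (20/6)² = 174.4, rounded up to 175, so 350 in total.
- With 20% attrition: 350 / 0.80 = 437.5, rounded up to 438.

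Both figures reproduce. They concern the PRWE, and this point does not alter them. The protocol states no power or precision for the SF-12.

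**2. Inputs for the SF-12.**

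- SD = 10: the population norm in the SF-12 section, taken as the SD at follow-up (assumption).
- n = 175 per arm: the evaluable number planned for the PRWE, borrowed here (assumption). It may be generous, because the abridged telephone questionnaire guarantees only the primary outcome and the EQ-5D.
- r, the correlation between baseline and follow-up SF-12: not in the protocol. Values of 0.2, 0.3 and 0.5 are assumed, with 0.7 shown as a high case.

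**3. Without a baseline.**

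- SE = 10 × √(2/175) = 1.069
- 95% CI half-width = 1.96 × 1.069 = 2.10
- Difference detectable with 80% power = (1.960 + 0.842) × 1.069 = 3.00

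**4. With a baseline covariate.** Adjustment multiplies the variance by (1 − r²), so the SE and half-width are multiplied by √(1 − r²). The equivalent gain in sample size is 1/(1 − r²).

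| Assumed r | √(1 − r²) | CI half-width | Narrower by | Detectable difference | Equivalent sample size |
|---|---|---|---|---|---|
| none | 1 | 2.10 | – | 3.00 | 1.00 |
| 0.2 | 0.980 | 2.05 | 2% | 2.93 | 1.04 |
| 0.3 | 0.954 | 2.00 | 5% | 2.86 | 1.10 |
| 0.5 | 0.866 | 1.81 | 13% | 2.59 | 1.33 |
| 0.7 | 0.714 | 1.50 | 29% | 2.14 | 1.96 |

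This treats one time point at a time and ignores the three covariates already in the model. The absolute widths depend on the SD and n; the percentage gain depends only on r.

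**The case against.** A reader might infer that a planned analysis cannot be carried out, or that the SF-12 schedule contradicts the analysis section. The documents do not support this. The baseline rule opens with a condition, "Where available, baseline values of the dependent variable will also be included as a covariate in the models", which allows for outcomes that have no baseline. The SF-12 models run as specified.

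A reader might also infer that a chance imbalance in prior health would be mistaken for a treatment effect. That goes too far. Allocation is randomised and concealed, the comparison is unbiased, and an interval from a model without a baseline already includes the uncertainty due to chance imbalance. What is missing is the chance to adjust for such an imbalance and narrow the interval.

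Three further objections carry weight:

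- **The gain may be small.** At r = 0.3 the half-width falls by 0.10 points on a scale with SD 10. Patients enter within two weeks of an acute fracture, so a post-injury score would partly reflect the injury and could correlate weakly with later health. The PRWE is collected for both before and after injury; a baseline SF-12 would likewise need its reference period stated.
- **The EQ-5D substitute is not equivalent.** It includes pain and usual activities, which the fracture would affect, and the protocol gives no correlation with the SF-12. The gains tabulated for an SF-12 baseline do not carry over to it.
- **Leaving out a generic questionnaire can be defended on patient burden.** The baseline form already carries the PRWE for two periods and the EQ-5D.

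These points limit the size of the benefit. None shows harm from either remedy.

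**Conclusion.** The point holds as a minor design limitation. On the text, neither SF-12 summary can be adjusted for its own baseline, and both models rest on age, displacement and hand dominance. The cost is precision alone: a half-width of 2.10 points, against 2.05 to 1.81 for an assumed correlation of 0.2 to 0.5, or about 2% to 13% narrower. Without a correlation in the protocol, the loss cannot be pinned down further.

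The conclusion rests on the SF-12 section's list of times, because the Table 3 schedule was not readable in the copy reviewed. If that table shows a baseline SF-12, the SF-12 section should be corrected instead and the loss disappears. The primary outcome and the sample size of 438 are unaffected.

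**What to change.** Add the SF-12 to the baseline form completed before randomisation, state whether the answers refer to before or after injury, and enter the score as the covariate that the existing rule already allows. List baseline among the SF-12 times.

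For patients already recruited, or if the form cannot change, pre-specify the baseline EQ-5D as a covariate in both SF-12 models before outcome data are examined. Its gain is not quantified and may be smaller.

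The cost is twelve more items at baseline, estimated at about two minutes per patient, and a minor form amendment. The EQ-5D covariate needs no new data.
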